### Intervention

After laparoscopic surgery, the subjects will be asked to lie in the supine position without a pillow, and without eating or drinking. They will begin a liquid diet on the second day after surgery. The two groups will receive XNKQAT intradermal needling or sham stimulation 6 h after the surgery. Treatment will be repeated every 12 h thereafter until a total of six treatments have been administered. Each treatment will last for 3 min. Each time, the intradermal needles (or sham needles) will be attached to the surface of the acupoints. Six hours after surgery, immediately before the first treatment, the first evaluation will be carried out. The subjects will be evaluated every 12 h thereafter until a total of seven evaluations have taken place. Acupoints will be located in accordance with the World Health Organization Standard Acupuncture Point Locations in the Western Pacific Region [20]. The acupoints used will be PC6, DU26, and SP6. The nurse administering the treatment will stand next to the subject’s bed and help them to find a comfortable supine position.

### Treatment (XNKQAT) group

This group of subjects will receive XNKQAT intradermal needling treatment at PC6 on both forearms, at SP6 on both ankles, and at DU26; that is, at a total of five acupoints (Fig. 3). After standard disinfection of the acupoints with 75% ethanol solution, the nurse will position the disposable medical intradermal needles (0.22 mm diameter × 1.5 mm length) perpendicular to the skin at the subject’s acupoints and then needle them into the skin. During the approximately 3-min treatment, the nurse will alternatively press the five intradermal needles for 15 s; a 20-s pause will occur between the repeated pressing intervals. To avoid injury to the skin or infection at the acupoints, the needles will not be twisted. The subject should feel a prick at the needled location. This study will use a visual analogue scale (VAS; Fig. 4) for pain [20] to determine the needle pressing force. Based on the VAS evaluation performed in the pilot trial, the pressing force will be limited to 40 mm. More importantly, in the XNKQAT, the manipulation standard of DU26 stimulation is “moistening of the eye,” that is, tear production (Fig. 5). Since the subjects will undergo a long pre-operative fasting period, excitation of the acupoints may trigger a hypoglycemic response. Therefore, it will be important to monitor the subjects’ faces during treatment to ensure they do not become pale or apathetic. If these signs occur, treatment will be stopped, the subjects’ blood glucose will be tested immediately, and appropriate management will be performed.

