### Control (sham) group

In the SH group, the acupoints will be selected as described above. Based on the successful pilot trial, the nurse will use adhesive tape that is similar to intradermal needle tape at the acupoints described above. However, they will not use needles or press the points. The number of sessions, and the duration of treatment, will match the procedure in the XN group. To ensure that subjects in the SH group feel fully cared for, they will be provided with health-related information and support (complication awareness, dietary direction, exercise training, and psychotherapy), and they will be more verbally engaged than the treatment group.

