##### Safety indicators

An adverse event is defined as at least four subjects suffering from the same symptom—such as local skin pain, itching, ulcers, bleeding, dizziness, or hypoglycemia—during the treatment and the follow-up period. Regardless of whether the unfavorable reactions or adverse events are related to the treatment, the researchers responsible for the treatment of the subjects will keep detailed records. Based on a statistical analysis of these events, XNKQAT safety will be evaluated.

If adverse events occur, the researchers will select an appropriate treatment method until the condition is stabilized. After the subject’s condition returns to normal, the researchers will decide whether further observation is required. If serious adverse events occur, the investigators will immediately report to the IRB and manage the subject’s condition appropriately.

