#### Statistical analysis

##### Analysis procedures

*Sample distribution:* We will describe the size and dropout rate of each dataset. Detailed reasons for any dropouts will be provided.

*Balanced comparison:* We will compare the general subject data and then evaluate comparability between the two groups.

*Efficacy analysis:* We will use the time until the first postoperative flatus as a primary outcome to assess the efficacy of XNKQAT by intradermal needling in the treatment of gastrointestinal dysfunction after laparoscopic surgery. We will calculate the average and standard deviation to describe the outcome and use an independent-samples *t* test to compare the two groups. Eight secondary outcomes (time until first postoperative defecation; level of abdominal pain, abdominal distension, and nausea; blood ghrelin level; vomiting; psychological status; and quality of life) will be compared between the two groups to determine the efficacy of XNKQAT intradermal needling. The mean and standard deviations of these parameters will be reported. To record the subjects’ psychological status, we will record their scores and determine their classification based on the standards mentioned above. To determine the time until the first postoperative defecation, we will use the same method as the time until the first postoperative flatus. To analyze abdominal pain, abdominal distension, nausea, vomiting, ghrelin level, and quality of life, we will use repeated measures analysis of variance (RMANOVA). Before RMANOVA, we will carry out a test of sphericity to ensure that the data are suitable for this method. If the data do not meet spherical symmetry requirements, we will use the ε correction factor to correct the degrees of freedom before applying RMANOVA. The Mann–Whitney *U* test or Spearman’s Rank correlation coefficient tests will be used to analyze the categorization standards for psychological status.

*Safety analysis:* According to the definition of adverse events, specific adverse events will be listed, along with their severity level, causes, and explanations. The number of adverse events, and the adverse event rate, will be described statistically. If they need to be compared between groups, the χ^2^ test or Fisher’s exact test will be used.

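### Active watching for hypoglycaemia, with glucose testing, is described only for the needled arm, so detection of this safety event may differ between arms

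*Protocol article*

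**What the plan says.** All references are to the protocol article.

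- **Treatment (XNKQAT) group.** Against the background of a long pre-operative fast, the protocol warns that "excitation of the acupoints may trigger a hypoglycemic response". Staff are to monitor subjects' "faces during treatment to ensure they do not become pale or apathetic". If signs appear, treatment stops, "blood glucose will be tested immediately, and appropriate management will be performed".
- **Intervention** (both arms). Subjects neither eat nor drink after surgery and start liquids on the second day. No watch for hypoglycaemia and no glucose test is described.
- **Control (sham) group.** Tape is applied at the same points, without needling or pressing. On what is matched, the section says: "The number of sessions, and the duration of treatment, will match the procedure in the XN group". No facial observation or glucose test is described. Sham subjects also receive information on complications, and "they will be more verbally engaged than the treatment group".
- **Safety indicators.** Dizziness and hypoglycaemia are among the named symptoms. Whether or not an event is related to treatment, "the researchers responsible for the treatment of the subjects will keep detailed records". An adverse event is defined as the same symptom in at least four subjects.
- **Blinding methods.** Subjects, evaluators and statisticians are blinded. Operators are not on that list.
- **Analysis procedures, safety analysis.** The number and rate of adverse events are described. "If they need to be compared between groups", a chi-squared or Fisher's exact test is used.

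**The concern.** A safety rate is comparable between arms only if events are looked for in the same way in both. Here the looking (facial observation) and the confirmation (a glucose measurement) are written into one arm only, for an event that the protocol itself names as a safety symptom. Fasting makes low glucose possible in either arm. An episode in a needled subject would be looked for and measured by written procedure. A similar episode in a sham subject depends on someone noticing it without that procedure.

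Who keeps the record adds to this. Blinded evaluators see every subject seven times, but the safety section gives them no role. Recording falls to those responsible for treatment, who on the natural reading know whether they needled or only applied tape.

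Safety is one of the trial's two stated aims. An excess of recorded hypoglycaemia in XN could then reflect needling, or closer observation, or both, and the data could not separate them. The primary outcome is not affected.

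**Working it through.** **1. The sections side by side**

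| Element | XN | SH |
|---|---|---|
| Fasting around surgery | yes | yes |
| Needling and pressing | yes | no |
| Watch for pallor or apathy described | yes | no |
| Immediate glucose test described | yes | no |
| General duty to record events | yes | yes |
| Complication information and extra verbal contact described | no | yes |

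The general duty to record is common. What differs is active looking and testing in one direction, and conversation about complications in the other.

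**2. Arm size, from the protocol's Sample size estimation**

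n = (1.96 + 0.84)² × (2.89² + 4.31²) / 4² = 7.84 × 26.9282 / 16 = 13.19, rounded up to 14. With 15% loss, 14 / 0.85 = 16.5, so 17 per arm and 34 in total. This reproduces the protocol's figure.

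**3. What unequal detection could do (illustration)**

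The protocol gives no rate of hypoglycaemia and no detection rate, so the inputs here are assumptions: the same true rate p in both arms, and detection of 90% in XN and d in SH. Then:

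- expected recorded cases are 17 × p × 0.9 in XN and 17 × p × d in SH;
- the apparent risk ratio is 0.9 / d, whatever p is.

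For p = 20%, XN has 17 × 0.2 × 0.9 = 3.06 expected recorded cases. The last two columns sum binomial probabilities over all outcomes with 17 subjects per arm.

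| Sham detection d | Expected recorded, XN v SH | Apparent risk ratio | Chance of Fisher P < 0.05 | Chance that at least 4 subjects are recorded in total |
|---|---|---|---|---|
| 90% | 3.06 v 3.06 | 1.0 | 1.8% | 88% |
| 50% | 3.06 v 1.70 | 1.8 | 3.8% | 72% |
| 30% | 3.06 v 1.02 | 3.0 | 7.1% | 60% |
| 10% | 3.06 v 0.34 | 9.0 | 13.1% | 45% |

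As sham detection falls from 90% to 10%, the chance of a false significant result runs from 0.6% to 1.2% at a true rate of 10%, and from 2.0% to 34.7% at a true rate of 30%.

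Two things follow. The main effect is a distorted comparison of rates; false significance is the lesser problem except at high event rates. And if the four-subject definition is counted across the trial, detection also affects whether hypoglycaemia qualifies as an adverse event at all.

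**4. The extreme case**

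Suppose 3 true cases in each arm, all found in XN and none in SH. The recorded rates are 3/17 = 17.6% and 0/17 = 0%. The two-sided Fisher P is 2 × C(17,3) / C(34,3) = 2 × 680 / 5984 = 0.23. Six true cases exist but only three are recorded, which is below four.

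**The case against.** The strongest reply has five parts.

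- **Needling is the stated trigger.** A reader might infer that the protocol blames fasting alone. It does not: it names excitation of the acupoints as the trigger and fasting as background. A precaution tied to needling belongs naturally in the needled arm. This stands as a reading of the text. It does not remove the problem, because the fasting is shared and the event is counted in both arms.
- **The duty to record covers both arms.** It applies during treatment and follow-up, regardless of cause, and one case report form holds all adverse event records. Nothing forbids testing a pale sham subject. This stands, so it would be wrong to infer that sham cases would go wholly unrecorded. The difference is in active looking and measurement.
- **The recorders may not be the operators.** The sections on the two arms say that a nurse delivers the intervention, whereas the safety section speaks of researchers responsible for treatment, who could be the ward clinicians. Unblinded recording is the natural reading but not a certain one.
- **The between-arm test is conditional.** A reader might infer that the safety conclusion rests on that test. The protocol makes it optional. The event counts and rates are reported in any case, and readers will compare them.
- **The direction is not one-sided.** Complication information and more conversation could raise symptom reporting in the sham arm. This stands for dizziness and other reported symptoms. For glucose-confirmed hypoglycaemia the written procedure points towards more detection in XN.

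Diabetes is an exclusion criterion, so the assumed event rates may be too high.

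**Conclusion.** The point holds in limited form. As written, the plan gives the needled arm an active search and a confirmatory measurement for a named safety event, and describes neither for the sham arm. Detection of hypoglycaemia may therefore be higher in XN than in SH. The size cannot be stated from the protocol. The apparent risk ratios of 1.8 to 9.0 rest on assumed detection of 90% in XN and 50% to 10% in SH.

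The contrast of 18% against 0% is an assumed extreme and should not be read as an expected result. It is far from significant (P = 0.23), and its three recorded cases would not meet the protocol's own four-subject definition. That the records are unblinded is probable, not established. For symptoms other than hypoglycaemia, the net direction of any bias is undetermined.

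The change is worth making because it protects a stated aim at very little cost.

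**What to change.** 1. Reconcile the sections Intervention, Treatment (XNKQAT) group, Control (sham) group and Safety indicators, so that safety observation and its recording are described identically for both arms at every session. What the clinical rule should be, including when treatment stops and what is tested, is for the sponsor to settle. The statistical requirement is only that observation does not depend on the arm.
2. At the seven evaluations already scheduled, have the blinded evaluators record a fixed list of systemic symptoms, such as dizziness and signs of hypoglycaemia, for every subject. After the first evaluation, which precedes treatment, the list should cover the interval since the previous one. Base any between-arm comparison of these symptoms on that record.
3. Leave needle-site symptoms (skin pain, itching, ulcers, bleeding) with the unblinded staff. If the evaluators asked about them, the answers could reveal the arm to the people who rate pain, distension and nausea.
4. State in Safety indicators which role keeps the event record and whether that role knows the allocation.

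The cost is a short checklist at visits that already take place and slightly more recording in the sham arm. What remains is that needle-site symptoms are still recorded unblinded and should be reported as such.

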**Fig. 3 Fig3:**
[figure not shown]
*Xingnao Kaiqiao* acupuncture technique and intradermal needle

**Fig. 4 Fig4:**

Visual analog scale

**Fig. 5 Fig5:**
[figure not shown]
Moistening of the eye under the intradermal needling

### Control (sham) group

In the SH group, the acupoints will be selected as described above. Based on the successful pilot trial, the nurse will use adhesive tape that is similar to intradermal needle tape at the acupoints described above. However, they will not use needles or press the points. The number of sessions, and the duration of treatment, will match the procedure in the XN group. To ensure that subjects in the SH group feel fully cared for, they will be provided with health-related information and support (complication awareness, dietary direction, exercise training, and psychotherapy), and they will be more verbally engaged than the treatment group.

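### The sham arm is planned to receive more engagement, and apparently a support package, that the treatment arm does not, so the contrast is needling minus extra support

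*Protocol article*

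**What the plan says.** The section on the control (sham) group describes adhesive tape at the same acupoints, without needles or pressing. On matching it says: "The number of sessions, and the duration of treatment, will match the procedure in the XN group". It then adds a support element with a stated purpose, "To ensure that subjects in the SH group feel fully cared for". The content is: "they will be provided with health-related information and support (complication awareness, dietary direction, exercise training, and psychotherapy". The sentence closes with a direct comparison of the arms: "psychotherapy), and they will be more verbally engaged than the treatment group".

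The section on the treatment group begins "This group of subjects will receive XNKQAT intradermal needling treatment at PC6 on both forearms, at SP6 on both ankles, and at DU26" and goes on to needling, pressing and monitoring. It mentions no information, exercise or psychotherapy component. The Intervention section, which covers both arms, deals with positioning, diet, timing of sessions and evaluations, and acupoint location. It mentions no such component either.

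Under Analysis procedures, the secondary outcomes include "psychological status; and quality of life) will be compared between the two groups to determine the efficacy of XNKQAT intradermal needling".

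**The concern.** A sham control is useful because the arms differ only in the element under test. Here the plan writes in a second difference: more conversation and, it appears, a package of support in the sham arm.

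Dietary direction and exercise training could plausibly act on bowel recovery, which is the primary outcome. Psychotherapy and attention bear directly on HADS, and on GIQLI, which has a psychological and emotional component. No analysis in the article separates the support from the needling, and with support tied to arm none could.

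The stake is what the result can mean. The trial sets out to assess needling, but the arm difference would carry both effects. A lesser issue is that a difference in care may give subjects a small clue to their allocation. Subjects and their families record the time of first flatus themselves.

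**Working it through.** **Which elements differ between the arms**

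| Element | XN arm | Sham arm | Basis |
|---|---|---|---|
| Needle and pressing | yes | no | explicit |
| Number of sessions, treatment duration | same | same | explicit |
| Verbal engagement | less | more | explicit |
| Health information, dietary direction, exercise training, psychotherapy | not described | yes | inferred from the stated purpose and from absence elsewhere |

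Write *d* for the true effect of needling and *c* for the effect of the extra support, both in hours by which time to first flatus is shortened. The expected difference between the arms is then *d* − *c*. It equals *d* only if *c* = 0.

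**The plan's own sample size**

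Inputs from Sample size estimation: two-sided α = 0.05 (1.96), power 80% (0.84), SDs of 2.89 h and 4.31 h, difference 4 h. That section calls the two SDs average times, but the formula and the pilot results in the Background show they are SDs.

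- Sum of variances: 2.89² + 4.31² = 8.352 + 18.576 = 26.928.
- n = (1.96 + 0.84)² × 26.928 / 4² = 7.84 × 26.928 / 16 = 13.19, rounded up to 14 per arm.
- With 15% loss: 14 / 0.85 = 16.5, so 17 per arm and 34 in total.

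The stated 34 reproduces and is not in dispute.

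**Illustration of what *c* does to power**

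The documents give no effect for the support, so *c* = 1 or 2 h is an assumption. With 14 evaluable per arm:

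- Pooled SD = √(26.928 / 2) = 3.669 h.
- Standard error of the difference = 3.669 × √(2/14) = 1.387 h.
- Two-sample *t* test, 26 degrees of freedom, two-sided 5%, noncentrality = (4 − *c*) / 1.387.

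| *c* (assumed) | Visible difference | Noncentrality | Power |
|---|---|---|---|
| 0 h | 4 h | 2.88 | 79% |
| 1 h | 3 h | 2.16 | 55% |
| 2 h | 2 h | 1.44 | 28% |

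A normal approximation gives 82%, 58% and 30%, with the same pattern.

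**The case against.** **The bias is conservative.** If the support helps recovery, it works against XN, so a significant advantage for XN on time to flatus would stand despite it. This holds. A reader might infer that no effect could be attributed to needling at all, and the documents do not support that. What is lost is the size of the effect and the meaning of a null or sham-favouring result. The direction is also only probable, since the documents give no information on what the support does.

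**The sham-only reading is partly inference.** This also stands. Only verbal engagement is expressly compared between the arms. The text does not deny information, exercise or psychotherapy to XN subjects. If both arms do receive them, the wording needs correcting, and the unequal engagement remains.

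**The extra attention makes up for the missing needling contact.** Equal attention is a legitimate aim. The plan specifies more attention than the other arm and adds components that go beyond contact.

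**Blinding.** A reader might infer that the unblinded nurse delivers the package, or that sham sessions run longer. Neither is supported: no provider is named, and the number of sessions and duration of treatment are stated to match. Nothing says subjects see the other arm's care. The clue to allocation is therefore minor.

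**The power loss is hypothetical.** The support effect is assumed, and 4 h is the plan's clinically significant difference, not its expected effect. The six-patient pilot means differ by 28.32 − 15.21 = 13.11 h. Losing 1 or 2 h of that would leave power near 100%. Six patients are weak evidence, but the power figures should not carry the point.

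**Conclusion.** The concern holds as a confounded contrast. By explicit text the sham arm receives more verbal engagement, and on the most natural reading it alone receives the support package. The trial as written estimates needling minus extra support.

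For time to flatus, the bias is probably against XN if the support helps. A positive result could be read as conservative, its size could not be taken at face value, and a null result would not distinguish ineffective needling from effective support. HADS and GIQLI are the most directly exposed outcomes, and the plan nevertheless uses them to judge the efficacy of needling.

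The size of the bias is unknown. The fall in power from 79% to 55% or 28% rests on an assumed support effect of 1 or 2 h, a 4 h needling effect, the pilot SDs and 14 evaluable per arm. It shows only that a sample size set at the minimum for 4 h leaves little room.

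**What to change.** 1. In the section on the control (sham) group, delete the clause saying that sham subjects are engaged more than the treatment group.
2. In the Intervention section, state that both arms receive the same information and support from one script, with the same contact time per session. If the XN arm already receives the package, say so there.
3. Record on the CRF, for each session, that the script was delivered.
4. Record the date of the change, so that subjects enrolled before and after it can be distinguished in a sensitivity analysis.

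The cost is protocol wording, a short script and a few more minutes of contact per XN session, with no extra visits. The Trial status section says recruitment is ongoing, so an amendment is needed. Some of the 34 subjects may already have been treated under the unequal arrangement, and the amendment cannot undo that for them.
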